#
[figure not shown]

# STAND UP FOR HEALTH: A FEASIBILITY CLUSTER RANDOMISED CONTROLLED TRIAL (RCT) OF A THEORY BASED INTERVENTION TO REDUCE SEDENTARY BEHAVIOUR IN CONTACT CENTRES

# Background and Scientific Rationale

## Sedentary behaviour as a public health problem

Sedentary behaviour is a serious occupational health hazard, linked with an increased risk of type 2 diabetes, cardiovascular disease, musculoskeletal issues, and poor mental wellbeing [1-6]. These risks are independent of physical activity [7, 8]. Conceptually, sedentary behaviour and physical activity are different [9], with each thought to pose health risks independent of each other [5, 10-12]. A review of behaviour change strategies used for sedentary behaviour reduction among adults [13] reported that interventions which showed the most promise in reducing sitting time were those that aimed to changed sedentary behaviour rather than increase physical activity. The reduction of sedentary behaviour is therefore not a consequence of effectively promoting physical activity and should be recognised independently when developing interventions, guidelines and legislation.

Workplace sedentary behaviour is placing a large burden on employers and the healthcare system. Many employees working in office-based environments become exposed to prolonged periods of inactivity in static seated postures, which are enforced by factors such as ergonomic set-up and workplace culture [14]. This sedentary behaviour can impact significantly on the daily lives and activities of workers. For example, musculoskeletal issues are one of the most prevalent occupational health problems for desk based workers and are a leading cause for disability worldwide [15-17]. Estimates of the prevalence of musculoskeletal symptoms in computer users are as high as 50 per cent [18]. Lower back pain in particular is associated with prolonged sitting [19, 20].

## Factors contributing to sedentary behaviour in workplaces

In a traditional office setting, high levels of sedentary behaviour and low levels of physical activity are a result of multiple causal factors, which include workload and social norms surrounding workplace behaviours [21, 22]. Multi-level interventions have previously been successful in reducing total [23] and prolonged [24] sedentary behaviour within this setting, though few studies have been effective at promoting physical activity [25] in the workplace and only a limited number of trials have reported success in managing long-term positive behaviour change [24]. At present, only a very limited number of research studies have sought to explore the reduction of sedentary behaviour or promotion of physical activity in the contact centre setting.

**Contact centres and organisational drivers**

Many organisations representing the contact centre industry are highly constrained by profit-based drivers, cost minimization, and economic outcomes based on productivity and high quantity customer enquiry resolution [26]. This has resulted in standardised work methods, removing the need for specific skills and reducing costs associated with employee training. The work itself can be isolating, and employees may view themselves as replaceable. These factors can also often influence organisational investment into workplace health initiatives; fears of cost-ineffective programmes and reduced productivity rates are commonly presented by senior team leaders within private contact centres [27].

Whilst emergent technology and customer expectations are important for shaping the nature of the work contact centres (e.g voice recognition, more use of social media) there is no anticipation that this will remove the necessity for contact centre agents to use a computer of some sort. There may be a trend to more remote working in the next few years, but it is likely that sedentary will still be an issue.

## Contact centres as a setting for a public health interventions

There are over with 6,200 contact centres in the UK, employing 734,000 agents [28] which is roughly 1 in 25 of the UK workforce. Scotland and the North East of England are home to some of the largest contact centres in Europe. Workplaces are often considered as homogeneous, but there are wide variations in terms of the demographics of the worker, the amount of worker autonomy, salaries, the environment (e.g. rigid workstations) and culture.

The staff demographic profile is different from other non-manual workplaces, with a younger workforce, lower wages, and a higher proportion of women and part-time workers. The call handlers (the highest proportion of contact centre staff) earn an average salary of £16,319 per year compared with the national average of £26,500 which puts them in the bottom third of earners [29]. In terms of gender, they are more likely to be female (60:40) [28] and ONS [30] data shows a reasonably consistent picture of a 70:30 split of full and part time employment [31]. Career progression is limited and even the most experienced of contact centre staff earn only slightly more than those with least experience. Turnover rates are high in UK contact centres with average attrition rates of 21% reported in 2017. Short-term absence rates are also high with 6.8% of agent workdays being lost to short-term sickness and unauthorised absences [32].

**Contact centres and health**

Due to their occupational nature, contact centres are currently one of the most sedentary working environments, with some members of staff reporting up to 95% of their shift spent sitting. The technology in contact centres prevents staff from regularly leaving their desk and many call handlers often report stressful work environments due to low workplace autonomy, strict supervision of individual performance and commission-based salary systems [33]. One in four members of contact centre staff regularly experience musculoskeletal problems with 22.4% of sick days lost to such problems [30].  A recent study found that a common factor for sedentary behaviour shared by contact centre agents, team leaders and senior staff included a considerable lack of knowledge and awareness of sedentary behaviour as a risk factor for poor health in highly sedentary workplaces [27]. Additionally, there was also a low level knowledge among staff of guidelines and recommendations relating to sedentary behaviour and physical activity in the workplace and often there is no reflection of this in organisational policies [27, 34].

In 2012, a study found that working in a contact centre was associated with higher levels of sedentary behaviour than other office-based work [4]. Another study [35], hypothesised that the culture and policies of a contact centre may differ from other office-based work and thus present a unique setting.

As well as being a highly sedentary workplace, work in contact centres has been described as ‘constrained’ work, where opportunities for enrichment and intrinsic reward are apparently limited [26]. Contact centre agents have voiced concerns over job security, performance monitoring and a desire for increased autonomy over their working practices as influential factors for their motivation to participate in strategies to reduce sedentary in the workplace [27]. However, organisational pressures to maintain high levels of productivity and meet targets frequently work against organisational investment into health and physical activity programmes within some contact centres. This is often due to perceptions that these activities will reduce the agents’ call making time and lead to productivity losses [36]. One study reported that leaders and senior staff had ‘identified a conflict between promoting productivity and targets to call agents, while encouraging them to move more and sit less’ [27].

**Workplace intervention research to reduce sedentary behaviour**

Over the last 5-10 years there have been a number of systematic reviews of workplace interventions to increase physical activity and reduce sedentary behaviour [35, 37-39]. Most recently a systematic review of environmental interventions in workplaces (e.g. sit-to-stand desks) found evidence of significant reductions in sedentary behaviour in 14 out of 15 studies [38]. The most effective interventions were multi-component, targeting more than one level of the socio-ecological framework. In 2016, a systematic review assessed the effectiveness of white-collar workplace interventions to reduce sedentary time [39]. It similarly found that multi-component interventions had the greatest effect. Both reviews [38, 39] recommended a need to assess whether policy-based measures or organisational change could further increase effectiveness. One study assessed the effect of sit-stand desks and ergonomic awareness on reducing sedentary behaviour in 15 Swedish contact centres [40] and found that working at a sit-stand desk was associated with a slightly greater reduction in sitting time as opposed to sitting at a non sit-stand desk. Regular interruptions to sitting time during the work day have previously been found to significantly reduce discomfort in the lower back and fatigue levels in overweight and obese office workers, without affecting productivity [41]. Another study found that the use of standing desks led to significant reductions in upper back and neck pain in office workers [42]. A recent study exploring barriers to participation suggested that, ‘barriers occurred at multiple levels of influence, and support the use of ecological or multilevel models to help guide future programme design/delivery’ [43].

**Multi-component workplace interventions**

Given the specified need to address cultural and organisational factors affecting workplace behaviour, we developed and piloted Stand Up for Health (SUH, the intervention in this current proposal).  There are a limited number of other similar interventions but the evidence is still sparse and only one study, currently on-going, is UK based. This UK study is NIHR-PHR funded and is currently examining the effectiveness of the SMArT Work & Life intervention aimed at reducing sitting time of office workers [44].  Whilst this intervention is similar to our intervention in some aspects, Stand Up for Health specifically considers aspects of organisational change, targets contact centres, and takes a systems-based approach [45]. This takes into account the complexity of the context, resources and assets of specific contact centres.  The Stand Up Victoria study in Australia also had a multi-component intervention [46, 47]. However, height adjustable workstations were a main part of the intervention. Whilst we envisage some contact centres may take up this option, we recognise that not all contact centres have the resources, or desire, to implement them.  A third study in Perth, Australia, used a similar participatory approach to SUH but had no theoretical basis, and was only assessed at a 12 week timepoint [48].

**Contact centre research**

Many existing practices in contact centres contribute to prolonged sedentary behaviour. Introducing smaller environmental changes to some of these practices can considerably encourage reduced sitting times. Recommendations emphasise the importance of regularly breaking up sedentary time, with desk-based workers being encouraged to accrue 2-4 hours of standing and light activity daily during working hours [49]. However, workplace cultures can often contribute to perceived judgements of behaviour, where staff may feel uncomfortable going against ‘sitting-norms’ [50]. These perceptions can often deter employees from engaging in less sedentary practices during the working day. Stand Up for Health is designed to have organisational change as a key component of the intervention.

**Relevant policy and practice**

Policy regarding sedentary behaviour lags behind the evidence. A recent study reviewed current national and international occupational safety and health policy documents (e.g. guidelines, legislation, codes of practice) for their relevance to occupational sedentary behaviour [34]. The review found that many workplace and jurisdictions had legal frameworks which established a duty of care for occupational health but discovered that no occupational health and safety authority had a policy specifically targeting occupational sedentary behaviour. Although some existing policies have aspects relevant to sedentary behaviour in the workplace, the authors identified a need to address the emergent hazard of excessive occupational sedentary behaviour by developing specific policies for this issue. They also highlight a need to support workplace-based initiatives which aim to minimise sedentary behaviour and associated risks.

A number of awards exist across the UK which are designed to recognise and encourage efforts made by organisations to improve health and wellbeing in the workplace. These include the North East Better Health at Work Award (BHAWA) [51] in England and the Healthy Working Lives award [52] in Scotland. Although these awards have a number of categories for health promotion that can help mitigate some of the negative outcomes of excessive sitting time, reducing sedentary behaviour as a specific outcome is not acknowledged.

**Importance of this research**

Current UK workplace legislation means that many members of staff in contact centres receive remedial ergonomic support as a mitigation measure to reduce existing musculoskeletal issues, *only after* a chronic or musculoskeletal condition has been diagnosed [53]. However, current practices, compounded by workplace culture, inhibit initiatives that encourage contact centre staff to reduce sitting time [54]. Combined with the lack of policies from authoritative bodies that are specific to sedentary behaviour it is important that workplaces take proactive steps to develop their own organisational policies which include, and promote, opportunities for reducing occupational sitting time [34]. Given that contact centres are amongst the most sedentary workplaces [55], and employees report higher levels of stress and depression compared with other desk-based work [56], it is key that preventative approaches are implemented.

This work is currently needed to ensure healthier working policies are distributed equitably across all workplaces, not just those which have more worker autonomy and better working conditions. Creating healthier contact centres may be more difficult to do than for other workplace settings, which is why such an intervention is necessary. Also, building the capacity to develop and measure workplace-based interventions for health in contact centres is vital for developing a stronger business cases to encourage and enhance organisational uptake and buy-in.

# Study Aims and Research Questions

## Study Aims:

*Aim 1:* To test the acceptability and feasibility of implementing the Stand Up for Health intervention in contact centres

*Aim 2:* To assess the feasibility of using a cluster randomised controlled trial study design

*Aim 3:*To scope the feasibility of a future health economic evaluation of Stand Up for Health

*Aim 4:* Consider previous aims under the context of covid-19

### Research questions for Aim 1

1. What is the acceptability, feasibility, and utilisation of the various components of the intervention in a range of contact centres?
2. Does the programme theory and process of implementing the intervention work as intended?
3. Does the programme theory/intervention need adapting and in what ways?
4. Are there differences in delivery of the intervention, between different contact centres? If so what are the reasons for these?

### Research questions for Aim 2

1. Is the study design (cluster RCT) feasible for a confirmatory trial of an intervention to reduce sedentary behaviour in staff working in contact centres?
2. How many clusters and participants per cluster are required for a confirmatory trial?
3. What is the recruitment rate of participants in each cluster and how many are lost of follow-up (e.g. due to staff turnover)?
4. Are the range of study procedures (e.g. recruitment strategies and outcome measurement tools) feasible for a future confirmatory trial?
5. Are there differences in aspects of study procedures (e.g. uptake) between different contact centres? If so what are the reasons for these?
6. What are the preliminary estimates of the variability of primary (reduction of sedentary

behaviour in the workplace) and secondary outcomes within and between contact centres?

### Research questions for Aim 3

Is it feasible to provide estimates of the cost-efficiency of Stand Up for Health from a) an NHS and personal social services (PSS) perspective and b) and employers perspective.

# Design and methods

Feasibility study with a cluster RCT design (to address Aim 2) combined with a process and qualitative study (to address Aim 1), and an economic component (to address Aim 3).  As the intervention is implemented in a workplace, it is not possible to randomise at the individual level; therefore a cluster RCT is the only option.  We have explored the relative advantages and disadvantages of the stepped wedge and the cluster parallel group designs as the two most appropriate options. After much discussion we have decided that the design will be an **incomplete cross-forward cluster randomised trial** (see **Figure 1**). Our study design is unusual because it is not a standard stepped wedge design (it has lots of incomplete sections), but it is also not a standard wait-list control design because there are many cross-sectional comparisons which may not always be present in a wait list control design. Similar designs are increasingly being used in evaluation research and involve random and sequential crossover of clusters from control to intervention until all clusters are exposed [57]. It can be considered as an extension of the parallel cluster trial with a baseline period. Such a design makes it possible to achieve a phased introduction of the intervention. It combines pragmatism with a robust design, and the way the study is conducted has much in common with the parallel cluster trial. Such designs are considered to be appropriate when: 1) there is a belief that the intervention will be of benefit and unlikely to do any harm; 2) evaluating an intervention that will be implemented irrespective of evidence for effectiveness; or 3) when it will be logistically implausible to roll out the intervention simultaneously to all clusters [58]. This is an important consideration, since it would be very expensive to have enough equipment to loan out; we also wouldn’t be able to collect activpal data on half of the anticipated sample at one time-point. This design allows us to have a smaller number of individuals at each baseline assessment point thus smaller number of activpals and equipment and other resources required.

Whilst there continues to be debate over the design and its limitations (e.g. [59]), some of which are valid, evaluations of public health interventions often have to be pragmatic and take into account the stakeholders and context of the intervention involved (in this instance the contact centres). We argue that we need a pragmatic option for a number of reasons. First, it could potentially cause delays in the evaluation process if we waited until all contact centres were at the same stage of readiness for implementation. A structural/location/organisation change in one contact centre could delay the process. Second, it would be more costly and resource intensive to implement the intervention and collect baselines data in all the contact centres at a single time point. We have requested two researchers, but due to the spread of locations in Scotland and North East England, this would make implementation and data collection difficult and increase the potential for failure. Third, contact centres are already wanting to implement the intervention when they hear about it. It is unlikely to cause any harm. It has been implemented in one contact centre for over a year and only positive benefits have been reported. Journals such as The Lancet Global Health and Trials are publishing the results of such designs [e.g. 60, 61].

Setting

Ten contact centres with more than 100 employees in Scotland and/or the North East of England. These two areas have the highest rates of contact centres in the UK, employing up to 6% of the workforce in these regions [62]. We will consider other areas of England if there is interest and to ensure we have 10 contact centres taking part.

## Study population

As this is a cluster RCT, contact centres rather than the staff employed in the contact centres (including managers, supervisors and call handlers) will be recruited. All staff will have the opportunity to participate in the intervention. For the evaluation components, staff will have the option of taking part on an opt-in basis.

## Recruitment

Ten contact centres will be recruited and we aim to have them recruited by month three of the project. All staff in the contact centres who have been working in the contact centre will be invited (via email through their contact centre) to be involved in the evaluation of the intervention, with the aim of recruiting 27 individuals per contact centre per data collection period for the outcome data (270 in total), and 6-8 individuals per contact centre for the qualitative data collection (60-80 in total). Staff who are interested in participating will be sent an information sheet and consent form. It will be made clear that participation, or non-participation will not affect terms of their employment.

Retention

The average annual turnover (attrition) of contact centre staff is around 24% vs 15% for other industries.  This high rate of attrition has implications for the retention and follow up of participants. The high turnover is partly due to the number of students and people looking for short term work. Whilst this is a problem for the evaluation, it maybe more positive for the success of the intervention; it has the potential to impact on a range of people, enabling them to engage with health promoting activities that may encourage the development of lifelong habits.

One of the aims of this study is to determine the retention rates for a future study.  We have a number of strategies:

1. Staff will be incentivised (£5-10 gift voucher) to complete baseline and outcome data assessments
2. If staff leave the contact centre we will explore what methods it may be possible to use to follow them up (e.g., post, email, telephone) and evaluate the most effective
3. We will record data on length of time employed in the contact centres. This data will help us determine whether turnover is higher at the beginning of the employment period (which could impact on retention rates)

## Randomisation

Randomisation will occur in month three. The unit of randomisation is contact centres. A computer-generated block randomisation algorithm will be used to randomly allocate each contact centre to start the intervention at one of five time points, three months apart. Randomisation in this way allows us to introduce the intervention to each site in an unbiased way unrelated to time or the particular circumstances of each site. It also helps ensure there is approximate balance on average across all the intervention start times in terms of participant or contact centre characteristics.

Steps to minimise bias

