### Data collection timepoints

In order to minimise cost and participant burden for this trial, and since the main purpose of the trial is to test study processes and procedures, data will only be collected at a maximum of three occasions per site: at the end of the control period, and at 3 and 6 months after the end of the intervention in each site. Sites 1 and 6 will not have a control period, and sites 5 and 10 will not have a post-intervention period, in order to minimise the duration of the study for which there is no concurrent vertical comparison between control and post-intervention periods. To increase the response rate, participants will be paid a small amount (£5 end of control period and £10 for 3 months data) for taking part in data collection.

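### With two centres per start time and no named stratum, balance across start times holds only in expectation; blocking on one centre factor is a cheap improvement, not the correction of an error

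*Protocol*

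**What the plan says.** Under Recruitment, "Ten contact centres will be recruited". Under Randomisation, "A computer-generated block randomisation algorithm will be used to randomly allocate each contact centre to start the intervention at one of five time points", which gives two centres per start time. No stratification or minimisation factor is named. The same section then says of the randomisation: "It also helps ensure there is approximate balance on average across all the intervention start times in terms of participant or contact centre characteristics".

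The protocol expects centres to differ. In its account of contact centres as a setting it says "there are wide variations in terms of the demographics of the worker, the amount of worker autonomy, salaries, the environment", and under Design and methods the setting is "Ten contact centres with more than 100 employees in Scotland and/or the North East of England", with other areas of England possible.

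Under Data collection timepoints, measurements are taken "at the end of the control period, and at 3 and 6 months after the end of the intervention in each site", but "Sites 1 and 6 will not have a control period, and sites 5 and 10 will not have a post-intervention period". The Statistical analysis section fits site and participant as random effects, with calendar time, season and an intervention indicator as fixed effects, and calls the analysis exploratory. Progression criterion 1 nevertheless uses the 95% confidence interval for the primary outcome.

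**The concern.** Blocking on start time fixes the number of centres at each start. It does not balance region, headcount or type of work. With only two centres per start, chance is unlikely to do so in the allocation actually run.

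This design is more exposed than one in which every centre has before and after data. Sites 1 and 6 supply post-intervention data only, and sites 5 and 10 control data only. These four inform the effect only through contrasts with other centres. A random site effect shrinks such contrasts but does not remove them. A chance alignment of centre type with start order therefore moves the estimate and the interval that feeds criterion 1, and also the effect size carried into planning the next trial. Some of that error could be avoided at almost no cost.

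**Working it through.** **The plan's own figure.** 160/6 = 26.67, rounded up to 27 per centre per collection period; 27 × 10 = 270. Both reproduce. The 160 per arm cannot be rebuilt, because the SD, alpha, power and ICC are not given.

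**Balance in one allocation.** Take a two-level factor held by five of ten centres.
- Ways to place it: C(10,5) = 252.
- One centre of each type at every start: 2^5 = 32, and 32/252 = 12.7%. The other 87.3% leave at least one start with two centres of the same type.
- Intervention-only pair (1, 6) all of one type and control-only pair (5, 10) all of the other: 2 × C(6,3) = 40, and 40/252 = 15.9%.
- These two pairs have the same composition in 6 + 6 + 4 × 20 = 92 allocations, so they differ in 160/252 = 63.5%.

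**How much enters the estimate.** The calendar is inferred from Randomisation, Duration of the intervention and Data collection timepoints. Starts are at 0, 3, 6, 9 and 12 months; the control measurement is at the start (not sites 1 and 6); post measurements are 6 and 9 months after the start (not sites 5 and 10). That gives 24 site-periods, 8 control and 16 post.

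The model has site and participant random effects, categorical time and the intervention indicator, and is fitted by generalised least squares with the same 27 people at each round. Participant share means the stable part of within-centre variance; it and the ICC are assumed.

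Let w be the net weight of each site in the intervention estimate; the ten weights sum to zero. Over all 252 allocations the mean shift is 0, and the root mean square (RMS) shift per unit of stratum difference is √[(10/36) Σw²].

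Example, ICC 0.05 and share 0.5: the weights by start time are 0.146, 0.087, −0.013, −0.067 and −0.153, each for two sites. So Σw² = 2 × 0.0570 = 0.114, and √(0.2778 × 0.114) = 0.178.

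| ICC | Participant share | RMS shift | Largest shift | SE ratio, blocked and adjusted, if block explains 30% / 50% of between-centre variance |
|---|---|---|---|---|
| 0.02 | 0.3 | 0.235 | 0.61 | 0.956 / 0.924 |
| 0.02 | 0.5 | 0.212 | 0.55 | 0.961 / 0.933 |
| 0.05 | 0.3 | 0.204 | 0.52 | 0.936 / 0.885 |
| 0.05 | 0.5 | 0.178 | 0.45 | 0.944 / 0.898 |
| 0.10 | 0.3 | 0.165 | 0.42 | 0.931 / 0.870 |
| 0.10 | 0.5 | 0.139 | 0.35 | 0.941 / 0.888 |

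The typical shift is thus 14-24% of the stratum difference. The largest shift occurs in 4 of 252 allocations (1.6%). With one centre of each stratum at every start, the shift is exactly 0. If the block explains nothing, the SE ratio is 1. In a version without the participant effect, linear time plus season gave slightly smaller shifts than categorical time.

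**In minutes.** Assume SD 130; the plan's 160 per arm and 45 min imply 124-144 at 90-80% power, two-sided 5%, ignoring clustering. Two strata of five that explain a fraction f of between-centre variance differ by D = 2 × 130 × √(f × ICC).
- ICC 0.05, f = 0.5: D = 41.1 min and the RMS shift is 0.178 × 41.1 = 7.3 min/day, against an SE of 16.9.
- Lowest combination (ICC 0.02, f = 0.3, share 0.5): D = 20.1, shift 4.3.
- Highest (ICC 0.10, f = 0.5, share 0.3): D = 58.1, shift 9.6.

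The SEs over this range are about 15-20 min/day.

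**Same variance, not an extra harm.** √(16.9² − 7.3²) = 15.2, which is the SE after blocking and adjusting (0.898 × 16.9 = 15.2). The shift and the SE reduction are two views of one component.

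**The case against.** A reader might infer that the balance statement is false and that centre differences bias the effect. The documents support neither. The statement is hedged and claims balance over repeated randomisations, which random allocation delivers; the mean shift over all allocations is exactly zero. The planned site random effect counts between-centre variation in the SE, and six of the ten centres have data in both conditions, so the effect stays identifiable even with fixed site effects.

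Nor should the size be pushed up by pairing a 45 min stratum difference with the highest leakage. At SD 130 and ICC 0.02 the whole between-centre variance is 0.02 × 16,900 = 338, while a 45 min difference needs 22.5² = 506. The largest possible difference there is 2√338, about 37 min.

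Other points also stand. The analysis is exploratory. A narrower interval does not by itself make criterion 1 easier to meet or better founded. The protocol does not define its blocks, and a randomisation plan or SAP could add a stratum. Region may not split evenly, and nothing shows that headcount predicts sitting.

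These limit the priority; they do not remove the case. A fixed-site analysis is a poor substitute, since in the same model it raises the SE by about 35-99%. Blocking costs nothing in the model SE if the chosen factor turns out to be uninformative.

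**Conclusion.** A cheap improvement, not an error in the Randomisation section. Balance across start times holds in expectation only. In the realised allocation a 5:5 centre factor is fully balanced with probability 12.7%, and typically 14-24% of its difference enters the estimate as chance error that the SE already includes. Blocking on that factor removes its contribution and lowers the SE by roughly 4-13% if it explains 30-50% of between-centre variance.

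The probabilities rest only on ten centres, two per start and a 5:5 split. The leakage and SE figures rest also on the assumed ICC, participant share and explained fraction and on the inferred calendar; the minutes rest further on the assumed SD.

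**What to change.** In Randomisation, allocate all ten centres in one run as two blocks of five, with one centre from each block assigned to each start time. Define the blocks by one centre factor known at randomisation: region if the recruited centres split about evenly, otherwise the five larger against the five smaller by headcount. Pass only the coded block to the statistician, so that blinding to centre identity is kept. Add block as a fixed effect to the model in Statistical analysis. Reword the balance sentence to claim realised balance for the blocking factor only, and balance in expectation for everything else.

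Cost: a few words, one coded field and one degree of freedom, which matters a little with ten centres. All ten centres must be in hand when randomisation is run; Recruitment aims for this by month three, the month set for randomisation. Centre differences outside the blocking factor stay unbalanced. No extra participants, visits or staff are needed.
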